**1. Introduction**

After gastric bypass many patients suffer from early and/or late dumping syndrome as a reaction to carbohydrate rich meals. Gastric emptying after bypass is accelerated and nutrition enters the intestine faster, which leads to osmotically driven fluid shifts from the blood to the lumen. Late dumping occurs 1–3 h after eating, and is caused by hyperinsulinemia and is therefore characterized by symptoms of hypoglycemia like weakness, sweating, and dizziness. In most studies examining satiation hormones after oral glucose stimulation in non-operated patients, glucose loads of 50-75 g are used. For a measurable GLP-1 rise a threshold of 2 kcal/min into the intestine is needed. After gastric bypass gastric emptying is accelerated and less glucose is necessary to reach this threshold. In an ongoing pilot project in patients after gastric bypass, we examine whether glucose loads of 10 g and 25 g induce a reliable secretion of satiation peptides without dumping symptoms. The effect of these low concentrations of glucose on peptide release as well as gastric emptying of these glucose loads in normal weight and obese (non-operated) subjects is not yet know.

**2. Objective**

The aim of this study is to examine the effect of different concentrations of glucose on the release of gastrointestinal satiation peptides (PYY, GLP-1, GIP and ghrelin), as well as on plasma insulin, c-peptide, glucose and glucagon levels in healthy normal weight and obese humans. In addition we examine the gastric emptying rates of these different glucose loads.

**3. Methods**

**3.1 Study subjects**

12 healthy normal weight and 12 healthy obese subjects will be recruited. The screening procedure will include the following assessments: a medical interview and a full physical examination. Anthropometric measurements including weight, height, BMI, as well as heart rate and blood pressure will be recorded for all participants.

The following inclusion criteria are applied:

- Healthy normal weight subjects with a body-mass index of 19.0-24.5 or healthy obese subjects with a body-mass index of > 30
- Normal eating habits
- Age 18-40 years
- Stable body weight for at least three months

Exclusion criteria:

- Smoking
- Substance abuse
- Regular intake of medications (except for oral contraceptives)
- Medical or psychiatric illness
- Any abnormality detected during the screening procedure
- history of gastrointestinal disorders
- food allergies

The protocol will be submitted and approved by the Human Ethical Research Committee of the University of Basel. All subjects will have to give written informed consent.

**3.2 Study protocol**

**Overall design**

The study will be performed as a randomized, placebo-controlled, four-way crossover study, with each subject studied on four test days at least three days apart. The test trials will be identical in design except for the administered test solution (Figure 1).

**Experimental procedure**

Subjects will be admitted to the Phase 1 Research Unit of the University Basel in the morning after fasting overnight for at least 10 hours. An antecubital vein catheter will be inserted for blood drawing and a gastric tube will be swallowed. Fasting and postprandial blood samples will be taken from all participants. After taking the fasting samples (-10, -1 min), each patient will receive 300 mL of a test solution (tap water) that contains either 10 g glucose, 25 g glucose, 75 g glucose or nothing (placebo control) (Table 1). Each test solution is labeled with 50 mg ^13^C-sodium acetate for determination of gastric emptying rate. Blood will be drawn at the following time points: 15, 30, 45, 60, 90, 120, and 180 min. A 10 mL samples will be taken at each time point into tubes containing EDTA (6 µmol/l), a protease inhibitor cocktail (Complete^®^, EDTA-free, 1 tablet/50 ml blood; Roche, Mannheim, Germany) and a dipeptidylpeptidase IV inhibitor (10 μl/ml; Millipore Corporation, St. Charles, Missouri, USA). The total blood volume taken during one test day will be 100 mL. After centrifugation, plasma samples will be kept frozen at -20°C until analysis. Glucose and the following peptides will be measured: insulin, c-peptide, glucagon, PYY, GLP-1, GIP and ghrelin. For the determination of the gastric emptying rate, breath samples will be taken at -1, 15, 30, 45, 60, 75, 90, 105, 120, 150, 180, 210 and 240 min after intake of the test solution. Breath samples will be collected in foil bags.

**Figure 1 Nutritional composition of test solutions**

|  | **Amount of Sweetener (g)** | **Energy Content (kcal)** |
| --- | --- | --- |
| **tap water** | 0 | 0 |
| **glucose** | 10 | 40 |
| **glucose** | 25 | 100 |
| **glucose** | 75 | 300 |

http://www.caloriecontrol.org/sucralos.html

**3.3 Assessment of gastric emptying**

Gastric emptying rates will be assessed using the ^13^C-sodium acetate breath test. This test is an accurate, non-invasive, simple method without radiation exposure, and represents a reliable alternative to scintigraphy, the gold standard for measuring gastric emptying (1, 2). The test solutions will be labelled with 50 mg ^13^C-sodium acetate; the substrate is rapidly absorbed in the proximal small intestine, metabolized in the liver with the production of ^13^CO_2_ which is exhaled rapidly, thus, reflecting gastric emptying of nutrients (1, 2). Subjects will be asked to exhale through a mouth-piece to collect an end-expiratory breath sample into a 100 mL foil bag at certain time intervals. The ^13^CO_2_ breath content will be determined by non-dispersive infrared spectroscopy using an isotope ratio mass spectrophotometer (IRIS; Wagner Analysen Technik, Bremen, Germany). ^13^C-abundance in breath is expressed as relative difference (δ ‰) from the universal reference standard (carbon from Pee Dee Belemnite limestone). ^13^C-enrichment is defined as the difference between preprandial ^13^C-abundance in breath and ^13^C-abundance at the defined time points postprandially and is given in δ over basal (DOB, ‰). Based on these values, time to reach maximal emptying speed and areas under the curve of the responses will be calculated (2, 3).

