**4. Materials**

Glucosum anhydricum will be purchased at Hänseler AG, Herisau, Switzerland.

^13^C-Sodium Acetate will be purchased at ReseaChem GmbH, Burgdorf, Switzerland.

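### The gastric emptying AUC subtracts only a fasting breath value, and the 13C abundance of the glucose is not fixed, so a load-ordered bias in AUC is possible and could not be removed afterwards

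*Protocol*

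**What the plan says.** Comparing emptying across the loads is a stated aim. Section 2 of the protocol says: "In addition we examine the gastric emptying rates of these different glucose loads".

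The solutions are set in section 3.2 (Experimental procedure). Each 300 mL drink contains "either 10 g glucose, 25 g glucose, 75 g glucose or nothing (placebo control"), and the tracer does not vary with load: "Each test solution is labeled with 50 mg" of 13C-sodium acetate. Under Overall design, the four days differ only in the drink: "The test trials will be identical in design except for the administered test solution".

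On sampling, "breath samples will be taken at -1, 15, 30, 45, 60, 75, 90, 105, 120, 150, 180, 210 and 240 min", which gives a single pre-dose breath value and a window of four hours.

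Section 3.3 then says that enrichment "is defined as the difference between preprandial" abundance and the abundance at each later time point, reported as delta over basal (DOB). Both emptying outcomes come from this quantity: "Based on these values, time to reach maximal emptying speed and areas under the curve of the responses will be calculated". No other correction is described.

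On the glucose, section 4 gives the substance and the supplier: "Glucosum anhydricum will be purchased at Hänseler AG, Herisau, Switzerland". It gives neither the plant source nor the 13C abundance.

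**The concern.** DOB attributes every change in breath 13C after the drink to the acetate. Part of the glucose is also oxidised to CO2 during the four hours. If that glucose has a different natural 13C abundance from the subject's fasting breath, its CO2 shifts breath 13C as well, and the plan has no means of telling the two sources apart. The water session carries tracer but no glucose, so it cannot supply the missing background. No session gives glucose without tracer.

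The shift is nil with water and grows with the grams of glucose oxidised, so it runs in parallel with the factor under study. Randomisation and the crossover do not balance it, because it belongs to the treatment. Subtracting the fasting value does not remove it, because it arises after dosing. If it is present, a larger AUC after 75 g than after water could be partly or wholly an effect of the substrate and still be reported as a difference in emptying.

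**Working it through.** The protocol gives no figure for this effect, so there is none to reproduce. The check is a 13C mass balance.

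**Inputs from the protocol:** 50 mg of 13C-sodium acetate in every solution; 0, 10, 25 and 75 g of glucose; breath sampling to 240 min.

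**Physical constants:** molar mass of glucose 180.156 g/mol, with 6 carbons; molar mass of sodium acetate 83.03 g/mol with one 13C and 84.02 g/mol with two; natural 13C fraction about 0.0111.

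**Assumptions not in the documents:**
- Difference in 13C abundance between glucose and fasting breath (d): +14 per mil for a 13C-rich source such as maize, +5 as an intermediate value, 0 for a matched source.
- Glucose oxidised within 240 min at the 75 g load: 18 g (range 12 to 24 g).
- Acetate label recovered in breath within 240 min: 50% (range 40 to 60%).
- One or two 13C atoms per acetate molecule. The protocol does not say which.

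**Step 1, recovered label.**
- One 13C: 50 / 83.03 = 0.602 mmol; at 50% recovery, 0.301 mmol.
- Two 13C: 2 × 50 / 84.02 = 1.190 mmol; at 50% recovery, 0.595 mmol.

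**Step 2, excess 13C from glucose.** Excess = (g oxidised / 180.156) × 6000 mmol × 0.0111 × d / 1000.
- Carbon from 18 g: 18 / 180.156 × 6000 = 599.5 mmol.
- At +14 per mil: 599.5 × 0.0111 × 0.014 = 0.0932 mmol.
- At +5 per mil: 599.5 × 0.0111 × 0.005 = 0.0333 mmol.
- At 0: none.

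**Step 3, AUC inflation at 75 g** = excess / recovered label. CO2 output cancels from this ratio if it is constant over the session.

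| d (per mil) | One 13C per acetate | Two 13C per acetate |
| --- | --- | --- |
| +14 | 0.0932 / 0.301 = 31% | 0.0932 / 0.595 = 16% |
| +5 | 0.0333 / 0.301 = 11% | 0.0333 / 0.595 = 6% |
| 0 | 0% | 0% |

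**Step 4, range at 75 g, +14 per mil, one 13C.**
- 12 g oxidised and 60% recovered: 0.0621 / 0.361 = 17%.
- 24 g oxidised and 40% recovered: 0.1242 / 0.241 = 52%.

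**Step 5, ordering by load** (+14 per mil, one 13C, 50% recovery, same oxidised share of 18/75 = 24% at each load).
- 0 g: 0%.
- 10 g (2.4 g oxidised): 31% × 2.4/18 = about 4%.
- 25 g (6 g oxidised): 31% × 6/18 = about 10%.
- 75 g: 31%.

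If the oxidised share is 1.3 times higher at the two smaller loads, these become about 5% and 13%. The ordering is unchanged.

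**Step 6, wider sensitivity at 75 g.** With +15 per mil, 20 to 50% of the glucose oxidised and 40 to 60% label recovery, the inflation is 23 to 86% with one 13C and 12 to 44% with two. If the glucose is slightly poorer in 13C than breath (−1 per mil, 18 g oxidised, 50% recovery, one 13C), the sign reverses: 599.5 × 0.0111 × 0.001 / 0.301 = about −2%.

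**What the calculation leaves out.** The 18 g is treated as if all its CO2 were exhaled in the window; retention in the body would scale every figure down. A rise in CO2 output after the larger load would lower DOB and would not cancel if tracer and glucose CO2 appear at different times. The effect on time to maximal emptying speed was not computed.

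**The case against.** The strongest reply is that the documents do not show the problem exists in this trial. Everything turns on the isotopic difference between the glucose and fasting breath. The protocol names only a supplier, and with a matched source the bias is about zero. This stands. A reader might infer that the glucose is maize-derived, or that the AUC will in fact be inflated by 31%; the documents support neither. They show only that the plan does not exclude the bias and cannot correct for it.

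A reader might also infer that all the 13C in 75 g of glucose is counted as tracer. It is not. Only the excess over the fasting value enters DOB, and only from the part oxidised within the window.

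A third reply is that the reach is limited. Emptying is an additional aim, the hormone and plasma glucose outcomes are untouched, and AUC is one of two emptying measures. This also stands. Time to maximal emptying speed should be less exposed if the glucose CO2 appears mainly later in the curve, but that is an expectation, not a result.

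It could finally be said that this belongs in the SAP, or that a plant source is a mere purchasing detail. That is less convincing. The enrichment definition, the sessions and the material are all fixed in the protocol. No later analysis of these data can separate the two carbon sources without a glucose background or a known glucose abundance.

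**Conclusion.** The point holds in conditional form. As written, the plan credits to acetate any 13C shift that comes from oxidised glucose, and that shift follows the load. With 18 g of the 75 g oxidised and 50% label recovery, AUC at 75 g would be inflated by about 31% at +14 per mil and 11% at +5 per mil with singly labelled acetate, and by 16% and 6% with doubly labelled acetate. It would be about zero if the glucose matches fasting breath. Retention of glucose-derived CO2 would lower the non-zero figures. The isotopic difference, the oxidised amount, the label recovery and the number of labels are all assumptions. The structure is not: one fasting baseline, a fixed tracer dose, 0 to 75 g of glucose, no unlabelled-glucose session and no stated abundance.

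It does not follow that the emptying objective fails or that time to maximal emptying speed is invalid. This is an inexpensive safeguard to put in place before the glucose is bought.

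**What to change.** In section 4, require one glucose batch for all loads and all subjects, from a source whose 13C abundance is close to that of fasting breath (for example wheat, potato or beet). Have the value documented by the supplier or measured once before use.

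If such a batch cannot be had, state in section 3.3 that differences in DOB AUC between loads will not be interpreted as differences in emptying. Rely on time to maximal emptying speed as the less exposed measure, and note that its robustness is expected but not shown.

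The cost is a purchasing specification and at most one isotope measurement. A different supplier lot may be needed. Nothing changes for the subjects, and the loads, sessions and sampling times stay as planned.

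### Gastric-emptying AUC taken from unconverted DOB: it could confound a comparison of the weight groups with body size, and over the full 240 min it would barely reflect emptying rate

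*Protocol*

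**What the plan says.** Protocol section 3.3 fixes both the scale and the summaries of the breath test. Abundance is a relative difference "from the universal reference standard (carbon from Pee Dee Belemnite limestone"), and enrichment, the change from the pre-dose sample, "is given in δ over basal (DOB", ‰). The section continues that, from the DOB values, "time to reach maximal emptying speed and areas under the curve of the responses will be calculated (2, 3").

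Other relevant provisions:

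- The tracer dose is the same for everyone: "The test solutions will be labelled with 50 mg" of 13C-sodium acetate (section 3.3).
- Under Experimental procedure in section 3.2, "breath samples will be taken at -1, 15, 30, 45, 60, 75, 90, 105, 120, 150, 180, 210 and 240 min". No measurement of CO2 output is listed.
- The groups are 12 subjects with BMI 19.0 to 24.5 and 12 with BMI above 30, with no upper limit (section 3.1).
- Body size is recorded: "Anthropometric measurements including weight, height, BMI, as well as heart rate and blood pressure will be recorded for all participants" (section 3.1).
- The emptying aim in section 2 is by load: "In addition we examine the gastric emptying rates of these different glucose loads". The preceding sentence of that section sets the study in both weight groups.
- Section 3.5 names AUC and Cmax for the hormones and does not mention emptying.

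**The concern.** There are two separate difficulties with the AUC.

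**Scale.** DOB measures how strongly exhaled CO2 is enriched with 13C, not how much 13C is exhaled. The same label, emptied at the same speed, gives a lower DOB in a subject who produces more CO2, because it is more diluted. The two groups here are defined by body size and receive the same tracer dose. If obese subjects produce more CO2, comparing DOB-AUC between groups mixes emptying with body size.

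**Content.** An AUC carried on until nearly all the label has left the stomach measures total recovery. Fast and slow emptying then give nearly the same value, so it says little about the emptying rates that the objective asks for. This applies to the load comparison as well as to any group comparison.

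At stake are a group difference in emptying that is an artefact, and a load effect on emptying that the AUC fails to show.

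**Working it through.** The protocol gives no effect size, variance or power for gastric emptying, so there is no figure of its own to reproduce.

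**Step 1. How DOB-AUC scales.** DOB(t) is proportional to the 13CO2 excretion rate divided by total CO2 output. With a constant CO2 output,

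AUC(DOB) ∝ dose × fraction recovered ÷ CO2 output.

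The dose is fixed at 50 mg (section 3.3). With equal emptying and equal recovery, the obese/normal AUC ratio is therefore CO2 output (normal) ÷ CO2 output (obese).

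**Step 2. Size of the artefact.** The documents give no CO2 output. Assumption: it is proportional to body surface area (Mosteller, √(height in cm × weight in kg ÷ 3600)). At equal height the AUC ratio reduces to √(BMI normal ÷ BMI obese).

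| BMI normal | BMI obese | AUC ratio | Deficit |
|---|---|---|---|
| 22 | 31 | √(22/31) = 0.84 | 16% |
| 22 | 35 | √(22/35) = 0.79 | 21% |
| 22 | 40 | √(22/40) = 0.74 | 26% |
| 24.5 | 30 (lower bound) | √(24.5/30) = 0.90 | 10% |
| 19 | 40 | √(19/40) = 0.69 | 31% |

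The BMI limits 19, 24.5 and 30 come from section 3.1; 22, 31, 35 and 40 are chosen for illustration. Without the surface-area assumption, an obese CO2 output of 1.1, 1.2, 1.3 or 1.4 times normal gives a deficit of 1 − 1/1.1 = 9%, then 17%, 23% and 29%.

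**Step 3. What the scaling leaves alone.** A constant factor multiplies the whole curve, so the time of the peak does not move. In the model of step 4 with a half-time of 20 min, the peak is at 31 min in both groups while the AUC ratio is 0.793. That ratio is the same for AUC 0–60 and AUC 0–240, so shortening the window does not remove the body-size factor.

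**Step 4. AUC against emptying rate.** Model (assumed): exponential emptying at rate k = ln 2 ÷ half-time, followed by post-gastric processing at p = 0.03 per min. The share of eventually recovered label exhaled by time T is

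1 − (p·e^(−kT) − k·e^(−pT)) ÷ (p − k).

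At T = 240 this is 99.9%, 99.6%, 95.0% and 78.8% for half-times of 10, 20, 45 and 90 min. Applying the trapezoidal rule at the protocol's breath times (with zero enrichment at time 0), relative to a half-time of 20 min:

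| Half-time (min) | AUC 0–240 | AUC 0–60 |
|---|---|---|
| 10 | 0.98 | 1.23 |
| 20 | 1.00 | 1.00 |
| 45 | 0.96 | 0.63 |
| 90 | 0.80 | 0.37 |

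From 10 to 45 min the full-window AUC stays within 4%. The slight dip at 10 min comes from the trapezoidal rule on 15-min samples. AUC 0–60 roughly halves (0.63 ÷ 1.23 = 0.51).

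**Step 5. Chance of a spurious group difference.** Take 12 versus 12, no true difference in emptying, a two-sided test at 0.05 (section 3.5 gives the level but not the sidedness), and a t test with 22 degrees of freedom. With bias b and an assumed between-subject CV, SD = CV × √((1 + (1 − b)²)/2) and the noncentrality is (b/SD) × √(12/2). For b = 0.207 and CV 20%, SD = 0.20 × 0.902 = 0.180, the noncentrality is 2.81 and the probability is 0.77.

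| CV | b = 21% | b = 10% |
|---|---|---|
| 15% | 0.95 | 0.38 |
| 20% | 0.77 | 0.23 |
| 25% | 0.58 | 0.17 |
| 30% | 0.43 | 0.13 |

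**The case against.** The strongest reply is that the emptying aim is worded by glucose load, and section 3.2 makes the study a four-way crossover. Loads are then compared within a subject, whose own CO2 output cancels, apart from any change in CO2 output that the load itself causes. No section prescribes a test of DOB-AUC between weight groups. This stands, and it confines the scaling problem to a contrast that the protocol makes natural, by studying both groups, but does not spell out. It does not answer the second difficulty, because a full-window AUC is a weak measure of rate within subjects too.

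A reader might infer that the protocol leaves emptying rate unmeasured. It does not: time to maximal emptying speed is the first of the two named summaries, and a constant CO2 factor leaves it unchanged.

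A reader might also infer that the AUC is bound to be insensitive to rate. The protocol samples to 240 min but states no AUC window, and an early partial AUC would follow rate well. Even the full-window AUC falls to 0.80 at a half-time of 90 min.

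Finally, section 3.3 refers the calculation to its references 2 and 3, which were not available for this review, and a statistical analysis plan may exist. Either may contain a conversion. What can be said is that the protocol's own text takes DOB as the basis and states no conversion.

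**Conclusion.** The point holds in limited form. As written, the emptying AUC comes from an isotope ratio after a fixed tracer dose. If obese subjects produce more CO2, a normal-weight versus obese comparison of that AUC is confounded by body size. The deficit would be about 10% to 31% (21% at BMI 35 versus 22) with identical emptying.

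That range rests on CO2 output proportional to body surface area, equal height, equal label recovery and the BMI pairs shown; obese BMI has no upper limit. It would be too strong to state a downward bias as fact, since the documents give no CO2 output for either group.

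Independently, if the AUC covers the full 240 min, it mainly reflects total label recovered and hardly distinguishes half-times between about 10 and 45 min under the assumed model. This also weakens the comparison of loads. The change is worth making: the AUC is a named outcome that can mislead, and the data for a better one are already collected.

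**What to change.** Amend section 3.3 as follows.

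1. Base emptying conclusions, for loads and for any contrast between weight groups, on timing parameters: the planned time to maximal emptying speed, plus half-emptying time from a curve fitted to cumulative recovery. A constant CO2 factor cancels in both, so neither needs a body-size correction.
2. If an AUC is kept, express it as percent of 13C dose recovered, using CO2 output estimated from each subject's recorded weight and height, and state an early window for it.
3. Do not compare raw DOB-AUC between weight groups.

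If references 2 and 3 are meant to supply the conversion, one sentence saying so, with the window, would settle the scale question.

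The cost is a curve fit on breath data already planned. No extra samples or visits are needed. For the AUC only, the result would rely on predicted rather than measured CO2 output.

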**3.4 Laboratory Analysis**

*Active GLP-1, total GIP and PYY* will be measured by an Immunological Multi-Parameter Chip Technology (Roche Diagnostics GmbH, Penzberg, Germany). The intra- and inter-assay coefficients of variation are below 9.5% and 10.0%, respectively.

*Total ghrelin* will be measured with a commercially available kit (Millipore Corporation, Billerica, Massachusetts, USA). The intra- and inter-assay coefficients of variation are below 10.0% and 14.7%, respectively.

*Insulin, C-peptide and glucagon* will be measured with commercially-available ELISA kits. The ELISA kits for insulin and C-peptide will be purchased at Abnova, Taipei City, Taiwan; the ELISA kit for glucagon at Cusabio, Wuhan, China. The intra- and inter-assay coefficients of variation are below 8.1% and 8.5% (for insulin), below 6.7% and 9.9% (for C-peptide) and below 8.0% and 10.0%, respectively (for glucagon).

*Plasma glucose concentration* will be measured by a glucose oxidase method (Rothen Medizinische Laboratorien AG, Basel, Switzerland). The intra- and inter-assay coefficient of variation is below 2.9% and 3.9%, respectively.

